#### Process evaluation

A process evaluation conducted alongside the main trial will explore contextual factors and mechanisms of change that may impact on effectiveness and successful rollout of the intervention post-trial. Specifically, we will examine the contextual factors surrounding intervention delivery, which will include assessment of recruitment, retention, fidelity and adherence. The process evaluation will be developed according to the MRC guidance [52] and will make use of both quantitative data (including fidelity measurement, retention, adherence rates, time spent on different steps of the GSH programme) and qualitative data from interviews with therapists and participants pre- and post-intervention. Detailed information regarding whether the intervention was delivered as intended (fidelity) and the quantity of the intervention implemented (dose) will allow us to test the theorised mechanism of effect of GSH for PTSD (a combination of: psycho-education about PTSD; imaginal and in-vivo exposure work to achieve habituation to distressing images and avoided situations; cognitive work to identify and modify negative/distorted cognitions; and stress management skills to cope with anxiety and other symptoms) and whether certain factors appear to be more important than others.

### Sample size

As the study aims to demonstrate non-inferiority of GSH for PTSD compared to TFCBT, the power calculation considers the non-inferiority margin as opposed to the effect size. The non-inferiority margin will be 5 points on the 80 point CAPS-5 scale. A recent meta-analysis [11] indicates that the standardised mean difference between TFCBT and waitlist/usual care for the treatment of PTSD is − 1.62. This corresponds to 16.6 points on the CAPS-5. This means that if we demonstrate non-inferiority to within 5 points of the gold standard, we will also demonstrate superiority over wait list/usual care in line with International Conference on Harmonisation Harmonised Tripartite Guideline (Statistical Principles for Clinical Trials) E9 (ICH E9) guidance for non-inferiority studies [53, 54].

Pilot work indicates an intraclass correlation coefficient of 5.6% at the therapist level at 10 weeks. At 22 weeks, however, there was no observable clustering of CAPS-5 scores amongst therapists. Given our primary outcome (CAPS-5) is measured at 16 weeks we have allowed for 1% clustering and recalculated the sample size. We have allowed for 20% attrition. On the basis of the anticipated average therapist cluster size being four, the design effect is 1.03, requiring a 3% inflation of the sample size. This results in a final sample size of 192 (inflated from 186) which provides 90% power (nQuery v7.0).

For the qualitative elements of the study, the sample size will be guided by preliminary analysis and constant comparison (comparing and contrasting themes from other interviews) during each data collection phase, until the research team is satisfied that there is data saturation and no new themes which are important to the research question arise [55]. However, it is helpful to have a guide to sample size for study planning. Based on previous research [56] we propose that interviews will be conducted with 10–20 participants and 8 therapists purposefully sampled from the different geographical sites.

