### Statistical methods

The primary analysis will be performed using analysis of covariance, predicting follow-up CAPS-5 score controlling for baseline CAPS-5 score and important patient characteristics (including all minimisation variables). This will be a complete case intention to treat analysis. Checks will be made to ensure there is no appreciable clustering of outcomes within therapists, but if such clustering exists the primary analysis will be hierarchical. The results will be summarised using point estimates, 95% confidence intervals and *p*-values. Since this is a non-inferiority design, we will be checking whether the confidence interval for the difference between arms lies entirely within the 5 point non-inferiority margin. Participants with missing CAPS-5 score at follow-up will have a CAPS-5 score estimated from available IES-R scores (this will involve building a prediction model using information from participants with both IES-R and CAPS-5 scores). We will explore differences in treatment effects by gender in a sub-group analysis by including an interaction term between treatment arm and gender.

A sensitivity analysis will use multiple imputation to account for missing data if the number of cases lost due to incomplete information exceeds 10%. Secondary outcomes include: CAPS-5 at 52 weeks, IES-R, WSAS, PHQ-9, GAD-7, AUDIT-O, MSPSS, EQ-5D, ISI, GSES, PTCI, adapted CSSRI-EU and CSQ-8. These are all continuous measures and will be analysed similarly to the primary outcome. Transformations will be explored to improve model fit if distributional assumptions are not satisfied. This will be assessed by visual inspection and formal fit statistics compared to decide on the transformation chosen.

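### At the SD the protocol implies, 192 participants give about 84% power for the planned 95% interval before baseline adjustment, against the stated 90%

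*Protocol article*

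**What the plan says.** All the planning figures are in the Sample size section of the protocol article.

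- Margin: "The non-inferiority margin will be 5 points on the 80 point CAPS-5 scale".
- Scale: a meta-analytic standardised mean difference of 1.62 between TFCBT and waitlist or usual care is translated into raw points: "This corresponds to 16.6 points on the CAPS-5".
- Losses: "We have allowed for 20% attrition".
- Clustering by therapist (ICC 1%, about four participants per therapist): "the design effect is 1.03, requiring a 3% inflation of the sample size".
- Result: "This results in a final sample size of 192 (inflated from 186) which provides 90% power (nQuery v7.0").

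The Statistical methods section sets the decision rule. The primary analysis is an ANCOVA adjusting for baseline CAPS-5. On reporting it says: "The results will be summarised using point estimates, 95% confidence intervals and" p-values. Non-inferiority is then read from whether the confidence interval stays inside the 5-point margin. No 90% interval and no one-sided interval appears anywhere in the article.

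**The concern.** A sample size for non-inferiority has to be computed at the error rate of the interval that will decide the question. A two-sided 95% interval tests the margin at one-sided 2.5%. The section's own conversion fixes an SD, and at that SD the printed totals fit one-sided 5%, not 2.5%. If that is how they were obtained, the calculation and the decision rule use different error rates. The chance of failing to show non-inferiority when the two treatments are truly equal would then be about 16%, rather than the 10% that readers and funders are told.

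**Working it through.** **Inputs.** From Sample size: margin 5, total 192 (186 before clustering), attrition 20%, design effect 1.03. From Allocation and blinding: ratio 1:1. From Statistical methods: 95% interval, hence one-sided alpha 0.025. Assumption: true difference 0, since no expected difference is given.

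**Implied SD.** SD = 16.6/1.62 = 10.25. Allowing for rounding of both figures, the range is 16.55/1.625 = 10.18 to 16.65/1.615 = 10.31.

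**Reproducing the plan's totals.** Required n per arm for 90% power (noncentral t), divided by 0.8 for attrition and rounded up:

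| SD | One-sided alpha | n per arm | After attrition, total |
|---|---|---|---|
| 10.25 | 0.05 | 73 | 2 × 92 = 184 |
| 10.3 | 0.05 | 74 | 2 × 93 = 186 |
| 9.3 | 0.025 | 74 | 2 × 93 = 186 |
| 10.25 | 0.025 | 90 | 2 × 113 = 226 |

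Then 186 × 1.03 = 191.6, which rounds up to 192. So both printed totals are recovered exactly at one-sided 5% with SD 10.3, which lies inside the rounding range. They are also recovered at one-sided 2.5%, but only with an SD near 9.3, which lies outside it.

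**Power of 192 at the implied SD.**

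- Effective n per arm = 192 × 0.8 / 2 / 1.03 = 74.6.
- Standard error = 10.25 × √(2/74.6) = 1.68.
- Margin / standard error = 5/1.68 = 2.98.
- One-sided 2.5%: 2.98 − 1.96 = 1.02, so power is 84.6% by the normal approximation and 84.1% by noncentral t. Over the SD rounding range the noncentral t figure runs from 84.6% (SD 10.18) to 83.7% (SD 10.31).
- One-sided 5%: 2.98 − 1.645 = 1.33, so power is 90.9% (normal) or 90.7% (noncentral t).

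**Size that would give 90% at one-sided 2.5%, unadjusted.** 90 per arm: 180/0.8 = 225, and 225 × 1.03 = 231.75, so 232.

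**Effect of baseline adjustment.** ANCOVA reduces the SD to 10.25 × √(1 − r²), where r is the baseline-outcome correlation. At one-sided 2.5% with 74.6 per arm (noncentral t):

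| r | Power |
|---|---|
| 0 | 84.1% |
| 0.3 | 87.3% |
| 0.4 | 89.8% |
| 0.5 | 92.8% |

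**The case against.** **The planning SD is inferred.** The 16.6 points serve to justify the margin against waitlist or usual care, and the section never says that this SD drove the power calculation. An SD of about 9.3, perhaps from pilot data, would give 186 at one-sided 2.5% with no alpha mismatch. This stands as a limit on certainty. It does not remove the problem, because 9.3 disagrees with the only SD derivable from the article, and the text would still need reconciling.

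**The planned analysis may recover the power.** The ANCOVA is fixed in the plan, and a correlation of about 0.4 would bring power back to about 90%. The plan also intends to estimate missing CAPS-5 scores from IES-R. At SD 10.25 and one-sided 2.5%, power would be 88.1% with 10% loss and 91.2% with none. Both points stand as possible gains. Neither is claimed in the sample size section, whose totals reproduce without them. The IES-R gain is also uncertain, because the primary analysis is described as complete case and an estimated score carries less information than an observed one.

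**Alpha and SD may be in the full protocol or SAP.** That is fair for an article, and their absence alone is not a defect. The point is that the printed figures do not agree with each other.

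**The 95% interval might mean a one-sided 95% bound.** The stated power would then hold, but nothing in the text says so.

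**Conclusion.** On the article's own conversion and its named interval, 192 participants give about 84% power, not 90%. This assumes SD 10.25, margin 5, true difference 0, 20% attrition, design effect 1.03 and no credit for baseline adjustment. The likeliest source is a calculation at one-sided 5%, but that is inference, because SD 9.3 at one-sided 2.5% yields the same totals.

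A reader might infer three stronger things that the documents do not support.

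- That the trial definitely lacks 90% power: the planned ANCOVA may supply it if the correlation is about 0.4 or more.
- That the false-positive risk of the primary conclusion is inflated: it is not, because the 95% interval is the stricter rule and no estimate is biased.
- That containment within the margin is a two-sided equivalence rule, which would cut power to about 69%: the trial's declared purpose is non-inferiority, so one limit is the fair reading.

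This is a should-fix matter: a misstated or unreconciled power figure, about 6 points at most on these inputs.

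**What to change.** Keep the two-sided 95% interval as the decision rule. The mismatch should not be resolved by loosening it to 90%.

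In the sample size section, state the SD and the one-sided alpha actually used. If the SD was not 10.25, give its source and reconcile it with the 1.62-to-16.6 conversion. Restate power for the 95% interval as about 84% unadjusted. If credit is taken for baseline adjustment, state and justify the assumed correlation: about 87% at 0.3 and 90% at 0.4.

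The cost is a few sentences and a less favourable stated power. No extra participants are needed.

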### Recruitment

Please refer to Fig. 2: Participant Timeline, for participant activity throughout the study. Prospective participants will be identified through Primary Care Mental Health Services (PCMHS) in South Wales, through IAPT services in England and psychological treatment services in Scotland. Three centres in Cardiff, Manchester and Musselburgh will initially oversee recruitment at up to 3 sites each and one site in London. More sites may be added if necessary. Primary care and other relevant workers in these services will be educated about the study and the eligibility criteria, and asked to identify and refer patients who may be experiencing PTSD to a single traumatic event and meet two of the other eligibility criteria (aged 18+ with regular access to the internet). They will be provided with a Summary Information sheet of the study, which they can discuss with the patient. With the patient’s consent, they will pass their contact details to the researchers by secure fax or a telephone call. The researcher will then telephone the patient to confirm they are over 18 years old with regular internet access, screen positive for PTSD on the Trauma Screening Questionnaire (TSQ) and do not appear to meet any of the exclusion criteria. If the patient is probably eligible, the researcher will send them a copy of the Participant Information Booklet to read before the appointment. If the patient is found to be ineligible, they will be referred back to the referring service. The referring services will be contacted regularly and will be provided with trial branded merchandise such as pens to remind them about the study.

**Fig. 2 Fig2:**
[figure not shown]
Participant Timeline. Participant activity throughout the trial

If necessary, to obtain the number of participants required, the Cardiff centre may also recruit participants through the National Centre for Mental Health (NCMH) cohort of participant volunteers. The cohort of over 9500 participants with lived experience of a mental illness currently includes 890 individuals with a diagnosis of PTSD, the majority of whom live in South Wales. A member of the NCMH team would contact potentially eligible individuals who have consented to being contacted about future research, to screen for eligibility and invite participation if eligible.

In addition to the methods described above, individuals referred to the local tertiary traumatic stress services will be screened by service clinicians and details of potentially eligible patients passed to the research team as described above. Information about the study will be communicated across all primary and secondary care services (including counselling services) in the recruitment areas and University Student Support Services (these were a source of recruitment in the pilot study). A limited number of leaflets will be available at key NHS services such as IAPT services, GP surgeries, Accident and Emergency services and outpatient clinics. We will publicise the trial publicly in conjunction with the NCMH communications team. This will include targeted press releases to local media with the offer of an interview with one of the study team, news items and advertisements on the NCMH website (www.ncmh.info), and a social media campaign to raise awareness of the study. We will seek to explore opportunities to recruit through the Criminal Justice System by linking with Victim Support, Sexual Assault Referral Centres (SARCs) and HM Court Services.

A screening log of all ineligible and eligible but not consented/not approached will be kept at each site so that any biases from differential recruitment will be detected.

### Allocation and blinding

Where possible, baseline measures will be collected electronically using an online database. Following completion of the baseline assessment, the database will inform the assessor that the participant is eligible for randomisation and the assessor will click the ‘Randomise Participant’ button. The database will allocate the participant to either GSH or TFCBT using pre-programmed software. This information will not be available to the assessor, who is blind to allocation, instead the database will email the trial manager who will inform the appropriate therapist. Individual randomisation will be conducted using an online minimisation algorithm generated by the trial statistician. The ratio will be 1:1. Minimisation will ensure balance between trial arms for gender, but will retain a random element and will be stratified by research centre.

It is not possible to blind the therapists or the participants given the complex interventions under investigation. However, the outcome assessors will be blind to treatment allocation and the therapists and participants will be asked not to discuss their allocation with the assessor. This will be stressed at the start of the interview and will minimise any potential bias the assessor may have when conducting the outcome assessments. To measure the success or otherwise of allocation concealment, the assessors will be asked to guess the participant’s allocation before and after each assessment. This will be recorded and compared to chance at the end of the study.

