#### TFCBT for PTSD

TFCBT for PTSD is one of the standard treatments adopted by IAPT in England and has been shown to be effective in RCTs in England [11, 33–36] and Northern Ireland [37]. There are a number of evidence based TFCBTs and, given the pragmatic nature of the trial, it will be permissible to use any one of them with individuals allocated to the TFCBT arm. An example of an evidence-based TFCBT is cognitive therapy for PTSD (CT-PTSD). CT-PTSD involves identifying the relevant appraisals, memory characteristics, triggers, and behavioural and cognitive strategies that maintain PTSD symptoms. CT-PTSD addresses these symptoms by: 1) Modifying excessively negative appraisals of the trauma and/ or its sequelae, 2) Reducing re-experiencing by elaboration of the trauma memories and discrimination of triggers, 3) Dropping dysfunctional behaviours and cognitive strategies, particularly those related to avoidance of triggers for intrusive symptoms. These are strategies that have the immediate aim of reducing one’s sense of current threat but have the long-term effect of maintaining the disorder, and are common in PTSD.

In this study, TFCBT will be delivered by experienced psychological therapists currently working in the IAPT or psychological services. They come from a variety of backgrounds, including mental health nurses, clinical psychologists and counsellors, and have varying levels of experience in working therapeutically with people with PTSD. All therapists will attend at least 1 one-day workshop on one of the TFCBT programmes. In addition, all study therapists are required to attend at least one and a half days training in CT-PTSD delivered by the group who developed CT-PTSD and to be assessed as being at least satisfactorily competent in the delivery of TFCBT by one of the two supervising authors who are experienced in TFCBT (NK, NR). The therapists will be given a treatment manual and will receive supervision once per month from one of two authors (NK, NR).

TFCBT will be delivered face-to-face to individual participants over the course of up to 12 sessions, each lasting 60–90 min. Appointments will take place at the service base. In-session treatment is augmented by daily homework assignments which participants are required to complete between sessions. They will be asked to complete the Impact of Events Scale-Revised (IES-R) at each session to measure and monitor their PTSD symptoms.

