Additional, non-IAPT measures will be administered at 16 and 52 weeks post-randomisation. Perceived social support will be measured using the Multidimensional Scale for Perceived Social Support [45], and the level of healthcare resource utilisation for health economic analysis will be determined by an amended version of the Client Socio-Demographic and Service Receipt Inventory European Version [46]. Changes in health related quality of life will be measured by the EQ-5D [47] and changes in sleep measured by the Insomnia Severity Index [48]. A short version of the Post-Traumatic Cognitions Inventory [49] and the General Self Efficacy Scale [50] will be collected to determine effects on cognitions and self-efficacy respectively. The Client Satisfaction Questionnaire [51] will be collected at 16 weeks post-randomisation only, to evaluate treatment satisfaction.

The IES-R will be collected at each therapy contact to provide clinical feedback and also to facilitate imputation for missing data, if required. How frequently it is collected will depend on the frequency of therapist contact, but is likely to be weekly in the TFCBT arm and fortnightly in the GSH arm.

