### Data Collection Methods & Data Management

All assessments will be conducted by research assessors who are either employed as Research Assistants by the centres involved, or are Clinical Studies Officers from the local Clinical Research Network. They will all receive training in rating the outcome measures. For the CAPS-5, this includes at least 1 day full training followed by rating a recording of an interview between an actor and an experienced interviewer. Assessors could be signed off if they score within 10% of the total score agreed by two of the authors (JB, CL), score differently on a maximum of four items and do not score more than one point different on any individual item. In order to ensure accurate ratings, assessors will receive video CAPS-5 interviews every 6 months to rate and return to JB and CL who will provide feedback.

Once they receive a referral, assessors will contact the potential participant by telephone to conduct a screening questionnaire made up of the TSQ and simple questions to assess inclusion criteria 1–3 and all of the exclusion criteria. Eligible participants will be sent a Participant Information Booklet and a daily diary and will be asked to monitor their symptoms for 2 weeks, as previous studies have found that this results in significant reduction in symptoms for some PTSD sufferers [33].

After the 2 week monitoring period, those still interested in taking part will be asked to attend a face-to-face appointment. Assessors, who have been trained in Good Clinical Practice (GCP) and receiving informed consent, will begin the consent process with the participant by reading through the Patient Information Booklet together and giving them to time to ask questions about the study. The assessor will then ask the participant to complete the triplicate study Consent Form if they are happy to do so. One copy will be given to the participant to keep. The assessor will then conduct the baseline assessment, which will assess inclusion criteria 4–6 and re-check criteria 2 (single event) and exclusion criteria 7. They will collect demographic data and the outcome measures previously outlined. Follow-up assessments will occur, as close as possible, to 16 weeks and 52 weeks post-randomisation. This will involve re-administration of the outcome measures and may be conducted face-to-face or on the telephone.

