### Health economics

An economic evaluation will be conducted from the perspective of the UK NHS and personal, social services. To determine the cost-effectiveness of GSH versus CBT for PTSD, and the extent to which it can be regarded as representing value for money, two analyses will be undertaken – one will assess the relative cost-effectiveness by estimating the incremental costs of achieving changes in natural units of outcome that commissioners, health care professionals, public health decision makers and service users find relevant (e.g. incremental cost of achieving a percentage improvement in PTSD symptoms as measured by CAPS5). The second analysis will use the EQ-5D utilities for a cost utility analysis estimating the incremental costs per quality adjusted life year (QALY) gained. The QALY gains will also be used in a net–benefit analysis based on accepted NICE ‘value for money’ thresholds.

The contributions associated with the GSH in relation to staff time and costs associated with training of therapists, along with materials and equipment used in the process associated with GSH development and implementation, will be collected during the trial by interviews with relevant finance staff, logged in physical units and translated into costs using published unit costs [e.g. [63, 64]. Resource utilisation of services prior to the GSH implementation, as a result of the intervention, and at follow-up relative to the control group, will be measured using the CSSRI-EU.

As the follow-up is at 52 weeks, no costs and outcomes will be subjected to discounting. Uncertainty around the cost and effectiveness estimates will be investigated by: probabilistic sensitivity analysis, using the incremental cost per QALY as the metric for this assessment measured against the NICE range of ‘willingness to pay’ thresholds between £20 k and £30 k per incremental QALY gained represented by cost-effectiveness acceptability curves [65]. a series of one-way sensitivity analyses to assess the impact of parameter variation on baseline estimates of the range of incremental cost-effectiveness ratios; and a set of alternative scenarios will be constructed, based on the findings from relevant studies of CBT for PTSD [33, 35–37] to compare the relative cost-effectiveness of GSH against different durations of CBT and supportive care .

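### The allocation guess taken after the whole visit cannot show whether the CAPS-5 was rated blind, because the same masked assessor also runs the visit in which service use is collected

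*Protocol article*

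**What the plan says.** All places are in the protocol article.

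- **Who assesses.** Data Collection Methods & Data Management: "All assessments will be conducted by research assessors". On follow-up it adds: "This will involve re-administration of the outcome measures and may be conducted face-to-face or on the telephone". No other person is named for any measure.
- **What is collected.** Outcomes lists, for 16 and 52 weeks, that "the level of healthcare resource utilisation for health economic analysis will be determined by an amended version of the Client Socio-Demographic and Service Receipt Inventory". It also lists a satisfaction questionnaire that "will be collected at 16 weeks post-randomisation only, to evaluate treatment satisfaction".
- **What the service-use inventory covers.** Health economics says that resource use before implementation, "as a result of the intervention, and at follow-up relative to the control group, will be measured using the CSSRI-EU".
- **How the arms differ.** TFCBT for PTSD: "TFCBT will be delivered face-to-face to individual participants over the course of up to 12 sessions, each lasting 60–90 min". The section on the Spring programme gives one meeting of an hour, four fortnightly meetings of 30 minutes and four brief calls or emails.
- **How masking is protected.** Allocation and blinding asks therapists and participants not to discuss allocation, and this is stressed at the start of the interview. Data Collection Methods & Data Management encourages participants to enter self-report questionnaires on the computer themselves, while assessors complete the rest of the interview.
- **How masking is checked.** Allocation and blinding has the assessor guess the "allocation before and after each assessment. This will be recorded and compared to chance at the end of the study".

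**The concern.** The masked rater is the main protection of the primary endpoint, and of the 52-week CAPS-5, which also carries a non-inferiority objective. Participants are asked to keep their allocation to themselves. In the same visit they complete an inventory that, as Health economics describes it, asks about service use arising from their treatment. An assessor who sees or hears those answers could work out the arm.

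The blinding check should show whether this harms the CAPS-5 rating. As timed, it brackets the whole visit and not the CAPS-5. If after-visit guesses beat chance, the trial team will not know whether its primary outcome was rated unmasked or whether the arm became apparent only after a rating made blind. In a non-inferiority trial this matters because a rater who expects the treatments to perform alike could draw the scores together and make non-inferiority easier to declare.

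**Working it through.** The plan gives no figure for masking, so there is none to reproduce. The check has four steps.

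**1. Could service-use answers point to the arm?** Scheduled therapist time, from the two intervention sections:
- TFCBT: up to 12 × 60 to 12 × 90 = 720 to 1,080 minutes.
- GSH: 60 + 4 × 30 = 180 minutes, plus four brief calls or emails.

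Answers that cover these contacts would usually identify the arm.

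**2. What can the two guesses tell apart?**

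| Guess before visit | Guess after visit | Reading |
|---|---|---|
| Chance | Chance | No sign of unmasking |
| Above chance | Any | Unmasking predates the visit, and so the CAPS-5 rating |
| Chance | Above chance | Unmasked during the visit, either before or after the CAPS-5 was rated |

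Only the third row is ambiguous, but it is the row that service-use answers would produce.

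**3. How large is the ambiguity?** Assume that about 154 participants are assessed (192 × 0.8 = 153.6), that before-visit guesses are at chance, and that assessors who are not unmasked guess at random. If a share u is unmasked during the visit, the proportion of correct after-visit guesses is q = u + (1 − u)/2, so u = 2q − 1. Let b be the number of points by which the arm difference would move if every participant were unmasked before the rating, with all shifts in one direction. The bias is then u × b. The range of b, 1 to 3 points, is an assumption.

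| q | u | One-sided exact tail against chance | Bias if unmasked before CAPS-5 | Bias if unmasked after CAPS-5 |
|---|---|---|---|---|
| 60% | 20% | 0.010 | 0.2 to 0.6 | 0 |
| 70% | 40% | 3 × 10⁻⁷ | 0.4 to 1.2 | 0 |
| 80% | 60% | 2 × 10⁻¹⁴ | 0.6 to 1.8 | 0 |

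The same test result fits both bias columns.

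**4. What would a bias do to the conclusion?** Inputs from Sample size: margin 5; SD = 16.6/1.62 = 10.25, implied by the two figures given there and not stated as such; 192 × 0.8/2 = 76.8 per arm. From Statistical methods: a 95% interval, so 2.5% in the relevant tail.

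SE = 10.25 × √(2/76.8) = 1.65. This leaves out the 3% design effect and any gain from baseline adjustment.

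At a true difference of 5, P(false non-inferiority) = Φ(−1.96 + shift/1.65):
- shift 0: 2.5%
- shift 0.5: Φ(−1.66) = 4.9%
- shift 1: Φ(−1.36) = 8.8%
- shift 2: Φ(−0.75) = 22.6%

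The shifts are averages over the arm difference and are assumed. By step 3, an average of 2 points lies above even the top of the 60% row.

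**The case against.** The case on the other side is substantial.

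- **Self-completion is already encouraged**, in a database with role-based permissions. This reduces what the assessor sees. It is not required, however, and assessors complete the other parts of the interview, so some exposure remains. A reader might infer that in telephone follow-up the assessor reads the items out. The article does not say so.
- **The order of measures is not stated.** A reader might take this as an error. An article may leave it to the full protocol, and if the CAPS-5 comes first, this route cannot touch the 16-week rating. The timing of the guess is stated, though, and stays ambiguous under either order.
- **The inventory's items are not shown.** It is an amended version, and the section on fidelity says that sessions attended or missed are recorded separately. That it reveals the arm is therefore inferred from the wording in Health economics. For the satisfaction questionnaire even that inference is missing: nothing in the article shows that its items reveal the arm.
- **The check does detect something.** A reader might conclude that it cannot detect unmasking at all. That goes too far. The before-visit guess finds unmasking that predates the visit, including carry-over from week 16 to week 52, and an after-visit guess at chance would be reassuring.
- **Bias could run either way.** A rater who favours face-to-face therapy would work against non-inferiority. The tolerance used to sign off assessors is a training standard and is not evidence of a shift between arms.

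**Conclusion.** The point holds as a cheap improvement to the blinding check. It does not show that the primary outcome will be rated unmasked. What the documents support is narrow: the masked assessor runs the visit in which service use is collected, that measure is said to cover use resulting from the intervention, and the guesses bracket the whole visit. An above-chance guess after the visit, with chance guessing before it, therefore cannot show whether the CAPS-5 was rated blind.

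The figures of about 5%, 9% and 23% illustrate what an average shift of 0.5, 1 or 2 points towards no difference would do to the 2.5% error rate. They rest on an implied SD of 10.25, about 77 per arm, and shifts whose size and direction are unknown.

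**What to change.** Amend Allocation and blinding and Data Collection Methods & Data Management so that, at each follow-up:

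1. The CAPS-5 is rated and locked in the database before any other measure.
2. The assessor records the allocation guess and the reason for it immediately after the CAPS-5. This is the guess compared with chance. The guess before the visit is kept.
3. The CSSRI-EU and CSQ-8 come last, entered where possible by the participant on a page that the assessor cannot see.
4. The before-visit guess at week 52 is used to report carry-over of unmasking from week 16. A different existing assessor is used at week 52 only where one is available.

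The cost is a reordered visit and one added database field. The database already restricts access by role and logs changes, which should make locking and hidden pages feasible. A general rule of changing assessors at week 52 is not needed and would not clearly be cheap, since the article itself names continuing assessor support as a risk.
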